### The assessment of current care

#### Design and methods

A retrospective medical record search based on the set of quality indicators will be performed in order to assess the Dutch gynaecologists’ adherence to the CS guideline recommendations. Adherence to these indicators will be quantified, as well as the variation in care and adherence between the participating hospitals. To gain insight into the current Dutch care compared to international care, the CS percentages of the different risk groups will be calculated according to the Robson classification (Table 1) [20]. Furthermore, the maternal mortality or severe acute morbidity (Table 2) [21], and perinatal mortality or serious morbidity (pH <7.00, Apgar 5 min <7, and NICU admission) will be noted. This study will provide us with information about current practice on CS in the Netherlands and insight into the effects on outcome of mother and child.

**Table 1 T1:** Ten-group classification according to Robson

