#### Study population and setting

In order to create a representative view of the current obstetrical care in The Netherlands, a multi-centre study will be carried out. Twenty hospitals of different Dutch regions will participate in this study, including university teaching hospitals, non-university teaching hospitals and non-university, non-teaching hospitals. The present study will take place in the setting of a Dutch Obstetric Research Consortium in which all the participating hospitals collaborate.

In the participating hospitals, data on basic obstetrical care and adherence to the quality indicators will be collected. Per hospital 100 women will be selected from the local database: 50 women who delivered by CS and a random set of 50 women who delivered vaginally in the same time period. Exclusion criteria will be a major fetal congenital malformality and fetal death prior to onset of delivery.

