#### Sample size considerations

Assuming an adherence to the guidelines of 75%, an alpha of 0.05, and a precision of the estimation of 5%, 300 patients must be included. However, this number has to be adapted to take clustering of data across clinicians and within obstetrical departments into account. Assuming an intra-cluster correlation (ICC) of 0.2 and 80 professionals in 20 hospitals, 960 medical records need to be analysed. In order to compensate for loss to follow-up or incomplete data, 1,000 women with a CS will be included in 20 hospitals within a timescale of three to four months. In order to enable the calculation of specific events, as described in ‘outcome measures,’ a random selection of 1,000 women with a vaginal birth will be included. Thus, there will be 2,000 participants, *i.e.*, 1,000 women after a caesarean delivery and 1,000 women after a vaginal birth. Sampling fraction will be adjusted to the fraction of women with CS in each individual hospital.

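### The 960 records allow for clustering by clinician but not, as stated, by department; the 5-point precision holds only if correlation between professionals within a hospital is about 0.004 or less

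*Protocol article*

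**What the plan says.** The point concerns the sample size paragraph for the assessment of current care in the Protocol article.

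- The starting figure assumes 75% adherence and "an alpha of 0.05", with "a precision of the estimation of 5%, 300 patients must be included".
- The paragraph then states that "this number has to be adapted to take clustering of data across clinicians and within obstetrical departments into account".
- The adjusted figure follows at once: "Assuming an intra-cluster correlation (ICC) of 0.2 and 80 professionals in 20 hospitals, 960 medical records need to be analysed".
- A margin is added for missing data: "In order to compensate for loss to follow-up or incomplete data, 1,000 women with a CS will be included in 20 hospitals". The study population section matches this: "Per hospital 100 women will be selected from the local database: 50 women who delivered by CS".

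Other sections treat hospitals as a source of variation. The design section for current care plans to quantify adherence "as well as the variation in care and adherence between the participating hospitals". The study population section chooses hospitals of different types and regions so that the results represent Dutch obstetric care. The sample size section of the later controlled before-and-after study names both professionals and hospitals as levels of clustering, and expects the larger part, not all of it, to lie with professionals.

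**The concern.** The paragraph promises an allowance for two levels of clustering, but it gives one intra-cluster correlation and one adjusted total. If the clinician level alone accounts for the whole step from 300 to 960, nothing is left for departments, and the text describes an adjustment that was not made.

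At stake is the precision claimed for adherence, the main outcome of this part. Women treated by different professionals in one hospital may still share local policy, staffing and case mix. If so, 960 records from 20 hospitals carry less information than 300 independent ones, and the 5% is too favourable. An interval calculated on the same clinician-only basis would be too narrow.

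**Working it through.** **Inputs from the sample size paragraph:** adherence p = 0.75; alpha = 0.05; precision d = 0.05; ICC = 0.2; 80 professionals; 20 hospitals; 960 records. Precision is read as the half-width of a two-sided 95% interval; the document does not state sidedness.

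**Step 1, the unclustered number.** n = z² p(1 − p)/d² = 1.96² × 0.75 × 0.25 / 0.05² = 288.1. The stated 300 looks like rounding up. At 300 the half-width is 1.96 × √(0.1875/300) = 4.9 points.

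**Step 2, the plan's 960.**

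- Records per professional: 960/80 = 12.
- Design effect for clinician clustering: 1 + (12 − 1) × 0.2 = 3.2.
- 300 × 3.2 = 960 exactly.

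Taking the 20 hospitals as the clusters does not reproduce the figure. At 960/20 = 48 records per hospital, the design effect is 1 + 47 × 0.2 = 10.4, and 300 × 10.4 = 3,120.

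**Step 3, adding a hospital term.** Let r be the correlation between records from the same hospital but different professionals, and keep 0.2 for records of the same professional. Each record then has 11 partners at 0.2 and 48 − 12 = 36 partners at r:

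DE = 1 + 11 × 0.2 + 36r = 3.2 + 36r

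Half-width = 1.96 × √(0.1875 × DE/960)

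The documents give no value of r, so those below are assumptions.

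| r (assumed) | DE | Effective n (960/DE) | Half-width, points |
|---|---|---|---|
| 0 | 3.20 | 300 | 4.9 |
| 0.01 | 3.56 | 270 | 5.2 |
| 0.02 | 3.92 | 245 | 5.4 |
| 0.05 | 5.00 | 192 | 6.1 |
| 0.10 | 6.80 | 141 | 7.1 |

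If the 0.2 is instead read as coming on top of the hospital correlation, the half-widths are slightly larger: 5.6 points at r = 0.02 and 6.5 at 0.05.

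**Step 4, how much r the plan can absorb.** Five points needs an effective n of 288.1.

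- With 960 records: (960/288.1 − 3.2)/36 = 0.0037.
- With 1,000 complete records (12.5 per professional, 50 per hospital): DE = 3.3 + 37.5r, and (1,000/288.1 − 3.3)/37.5 = 0.0046.

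**Step 5, whether more records would help.** With 80 professionals and 20 hospitals fixed, the N needed for 5.0 points is

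N = 0.8 / [1/288.1 − 0.2/80 − r(1/20 − 1/80)] = 0.8 / [0.003471 − 0.0025 − 0.0375r]

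- r = 0.01: about 1,340 records.
- r = 0.02: about 3,600 records.
- r = 0.05: the bracket is negative (0.003471 − 0.0025 − 0.001875), so no number of records suffices.

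**Step 6, indicators that apply to fewer women.** The data analysis section computes adherence separately for each indicator, among the women to whom it applies. As an illustration with an assumed share, take an indicator that applies to 25% of the records: 240 records, 3 per professional and 12 per hospital. With no hospital term, DE = 1 + 2 × 0.2 = 1.4 and the half-width is 6.5 points. At r = 0.02, DE = 1.4 + 9 × 0.02 = 1.58 and the half-width is 6.9 points.

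**The case against.** The arithmetic in the paragraph is correct for the level it covers, and several arguments limit what follows from the gap.

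- **Clustering may sit mainly with professionals.** The protocol expects this for the later study, and it is the only statement on how clustering divides. At r of 0.01 to 0.02 the half-width rises by only 0.3 to 0.5 points over the 4.9 points at r = 0. This stands, and the size of the loss rests on an assumed value. But a larger share for professionals does not mean none for hospitals, and the slack ends near 0.004.
- **Hospitals could be fixed strata.** If inference were limited to these 20 hospitals, variance between them would not enter the standard error. The protocol does not say this. It claims an allowance for departments and seeks a picture of Dutch care as a whole, so the reading cannot be excluded but fits poorly.
- **The overall precision is not the precision of each indicator.** This stands. In the illustration, restricting the denominator matters more than the hospital term, so the range above must be labelled as applying to an indicator that covers all records.
- **No interval method is stated.** This also stands. The article may leave it to a fuller plan, so a too-narrow interval is a conditional risk and not an error in the text.

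Two stronger readings are tempting. A reader might place the whole 0.2 at hospital level and conclude that precision is far worse; that conflicts with the stated expectation that professionals account for most of the clustering. A reader might also multiply 300 by a larger design effect and take the product as the records to collect. That product assumes added hospitals at 48 records each; step 5 shows that it does not hold within the planned 20.

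**Conclusion.** The concern holds as a mismatch between what the paragraph says was adjusted for and what the number contains. The factorisation is exact, so it is firm that 960 has no department term. The 5-point claim is supported only for a within-hospital correlation between professionals of up to about 0.004 (about 0.005 with 1,000 complete records).

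The size is less certain. Over assumed correlations of 0.01 to 0.10, the expected half-width is about 5.2 to 7.1 points in place of 5: a modest loss at 0.01 to 0.02 and a material one from 0.05. This rests on a two-sided 95% interval, equal numbers per professional and per hospital, hospitals treated as a sample of Dutch practice, and an indicator that applies to all records. It does not show that the study is too small for its descriptive purpose, and it is no reason to change the number of women.

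**What to change.** In the sample size paragraph for current care:

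1. State that the 960 records account for clustering at professional level only (ICC 0.2, 12 records for each of 80 professionals).
2. Replace the 5% claim with the expected precision over a labelled range of assumed hospital-level correlations: about 5.2, 5.4, 6.1 and 7.1 points at 0.01, 0.02, 0.05 and 0.10 with 960 records, for an indicator that applies to all of them. Add that indicators applying to fewer women will be estimated less precisely.
3. Where adherence intervals are reported, compute them with hospital as the top-level cluster.

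Leave the number of women as it is. The cost is a change of wording, a less favourable stated precision, and a choice of variance estimator for any intervals; data collection is unaffected.

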#### Data analysis

The frequencies of adherence per quality indicator will be calculated. This will be calculated by dividing the total number of women who apply for an indicator and for whom care was appropriate by the total number of women who apply for an indicator. For example, women with a child in breech presentation between 34 to 36 weeks of gestation, without contraindication for external cephalic version, should have been offered an external cephalic version. Adherence is the total number of women with a child in breech presentation between 34 to 36 weeks of gestation without contraindication for external cephalic version, in whom an external version was offered, divided by the total number of women with a child in breech presentation between 34 to 36 weeks of gestation without contraindication for external cephalic version.

### Barrier and facilitator study

#### Design and methods

To determine the barriers and facilitators that influence the decision to perform a CS for healthcare professionals and patients, a qualitative study will be performed. The setting for guideline implementation will be analysed. Focus group interviews will be held among healthcare professionals (obstetricians, residents, and midwives) to discover factors that determine the decision to perform a CS or not. The interviewer will explore the following categories of influencing factors: features of the guidelines itself; features of the target group of professionals who should use the guidelines; features of patients who have to accept or contribute to the use of the guidelines; features of the social setting and social network of the professionals; and features of the organizational, economic, and administrative context. Remarks by professionals will be classified into categories of potential determining factors following this theoretical framework. The ‘prevalence’ of the features mentioned in the focus group interviews will be quantified in a survey with questionnaires among the different professionals.

Similarly, depending on the outcome of the current care study, semi-structured interviews will be held with patients in a detailed study to discover relevant factors that influence the patients’ decision to choose a CS or vaginal delivery.

#### Study population and setting

In different hospital types (university, non-university teaching, and non-university non-teaching hospitals) interviews will be held among healthcare professionals (obstetricians, residents and midwives) as well as patients. Focus group interviews among 8 to 12 healthcare professionals will be planned. To assess whether the factors mentioned in the focus group interviews are structural, the ’prevalence’ of these factors will be assessed using a survey with questionnaires among obstetric gynaecologists, residents, and midwives in the Netherlands. The questionnaires will be sent to the professionals via email addresses we will obtain from the national professional organisations of both professions. Among patients, semi-structured interviews will be held. These patients will be selected in the abovementioned hospitals from the current care study. The interviews will be conducted with those women belonging to the non-adherence subgroups (such as breech, non-progressing labour, or maternal request) to whom a possible implementation should be directed. Approximately ten to fifteen women will be interviewed until no new information emerges during the interviews.

#### Outcome measures

The main outcome measures are the barriers and facilitators for adherence to the quality indicators for performing a CS.

#### Data analysis

Using Atlas, the qualitative software package, a qualitative analysis will be performed on the barriers and facilitators that are presented in the interviews among healthcare professionals and patients. The transcribed interview will be marked and coded with barriers and facilitators according to the framework used to structure the interviews: features of the guidelines, professionals, patients, social setting, and organization. These influencing factors will be quantified among all Dutch gynaecologists and midwives by means of questionnaires. The analyses of the questionnaires will be descriptive (*e.g.*, frequencies and means).

### Controlled before-and-after study

#### Design and methods

Based on the results of the current care study and the barrier and facilitator study, one or more target groups for a tailor-made implementation strategy will be identified. Target groups will be selected with focus on women with both a high incidence of the indicator (our hypothesis is that this will include, for example, non-progressing labour and previous CS) and low indicator adherence. A tailor-made implementation strategy will be developed in order to increase adherence to the CS quality indicators. This strategy will be executed and evaluated in a clustered CBA study in 12 hospitals (six intervention, six control hospitals) (see sample size calculation) in terms of effectiveness, experiences, and costs. It is likely that a strategy with different implementation elements is needed because several barriers for implementation of recommendations may exist at different levels. This will probably result in a combined intervention directed at the level of professionals, patients, and the organisation.

#### Study population and setting

The implementation strategy will be executed and evaluated in 12 hospitals (see sample size calculation) that also participated in the current care study: six intervention hospitals in which the newly developed strategy will be applied; and six control hospitals in which care as usual will be offered. In order to select these 12 hospitals, all 20 hospitals of the current care study will be categorized into university, non-university teaching, and non-university non-teaching hospitals (three categories). Within these three categories, possible hospital pairs will be made based on pre-intervention adherence to quality indicators and CS rates, as measured in the current care study. To get a sample representative for the Dutch setting, in total two university hospitals, six non-university teaching hospitals and four non-university, non-teaching hospitals will be asked to participate. Subsequently, the participating hospitals have to be assigned to the intervention and control group. This will be done per stratum and based on geographic region. The evaluation will include an effect, process, and cost analysis. Just as in de current care study, the effects will be measured both at medical outcome level (*i.e.,* CS rates and complication rates) and on guideline adherence level. Satisfaction with and applicability of the tailor-made implementation strategy for both patients and healthcare professionals will be measured in a process evaluation. Information regarding the process will be gathered in a qualitative study in the hospitals in which the implementation strategy was applied. Individual interviews will take place among the involved healthcare professionals and patients to gather data about experiences with the changed care. During the interview, they also will be asked about which elements of the tested strategy they specifically used to implement the evidence-based guidelines; how satisfied they are with the different elements; and their opinion about the feasibility of the different elements.

Furthermore, a cost analyses of the tested implementation strategy will take place with respect to three aspects: 1) the rate at which the guideline recommendations are already applied; 2) the costs of the implementation strategy (taking into account the development of the strategy, training of healthcare professionals, and possible extra costs regarding both time and medical costs) and 3) the effectiveness of the implementation strategy. In order to measure the effectiveness of the implementation strategy both the effects on medical outcome (*i.e.*, CS rates, complication rates) and adherence to CS quality indicators will be measured. The cost-effectiveness of the implementation strategy will be expressed as the incremental costs per extra patient treated according to the CS quality indicators, compared to the ‘do-nothing’ strategy.

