#### Data analysis

To assess the effectiveness of the implementation strategy, the proportion of patients that are treated in accordance with the guidelines before and after implementation of the guidelines in both the intervention and control hospitals will be measured. Medical outcome measures will include CS rates and maternal as well as neonatal complications related to vaginal delivery or CS. Multilevel multivariate analysis will be carried out to assess the independent effect of the implementation strategy on adherence to the CS quality indicators and medical outcome measures. A qualitative descriptive analysis will be done in order to evaluate the process. Furthermore, by means of a questionnaire, the experiences of healthcare providers and patient satisfaction with the implementation strategy will be evaluated, and the outcomes will be descriptive.

The costs analysis will be performed from a healthcare perspective. The costs of the implementation process will be calculated on the basis of the time and materials invested based on activity-based costing (ABC) approach, focusing on activities performed with costs accumulated at the activity level(s) of the healthcare implementation processes. The costs of implementation of the guidelines and consolidation consist of personnel and material costs. The input of resources will be assessed by collecting volumes of consumed resources, and multiplying these by the price of each resource unit. For collecting information on the input of the resources, registration forms will be completed by the people involved in the implementation and consolidation process. The prices of each resource unit will be based on standard costs [22], market prices, or self-determined costs. The medical costs used in de cost analysis will include CS rates and maternal and neonatal complications related to vaginal delivery or CS. The costs of implementation and costs of the changed medical care will be weighed against the proportion of patients that are treated according to the CS guideline, after implementation. The cost-effectiveness of implementation will be expressed as the incremental costs per extra patient treated according to the CS guideline, compared to the ‘do-nothing’ strategy (*i.e.*, no implementation, for which data before implementation will be used).

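### Hospitals in the before-and-after study are assigned by stratum and region, not at random, so the promised independent effect is not secured, although a random draw among the same 12 hospitals is feasible

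*Protocol article*

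**What the plan says.** The protocol article, under *Controlled before-and-after study – Study population and setting*, sorts the 20 hospitals of the current care study into three categories. To choose the 12 hospitals, "Within these three categories, possible hospital pairs will be made based on pre-intervention adherence to quality indicators and CS rates". The invitation is fixed by category: "in total two university hospitals, six non-university teaching hospitals and four non-university, non-teaching hospitals will be asked to participate".

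Allocation comes after that: "Subsequently, the participating hospitals have to be assigned to the intervention and control group". The rule is one sentence: "This will be done per stratum and based on geographic region". The result is "six intervention hospitals in which the newly developed strategy will be applied; and six control hospitals in which care as usual will be offered".

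The article does not mention random assignment of hospitals. It uses the word random only for sampling women who delivered vaginally. It gives no reason for using region.

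Under *Data analysis* of the same study, a multilevel multivariate analysis is to "assess the independent effect of the implementation strategy on adherence to the CS quality indicators and medical outcome measures". Region is not named there as an adjustment variable.

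**The concern.** A comparison of changes between arms estimates the strategy's effect only if both arms would have changed alike without it. Random assignment makes that true on average and gives a valid test. Assignment by region does neither.

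The before-measurement removes differences between hospitals that stay constant. It does not remove differences in how care changes between the two measurements, for instance through regional initiatives, referral patterns or local policy. The *Background* section shows that practice is moving: the national CS rate rose from 8.1% to 13.6% in about a decade, or 5.5 points. It does not say whether regions moved differently.

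If region decides the arm, any regional difference in trend enters the estimate in full, and more patients do not reduce it. A region term in the model would be collinear, or nearly so, with the arm. At stake is whether a difference between the arms can be credited to the strategy, which the *Discussion* ultimately wants to see adopted in all Dutch hospitals.

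**Working it through.** The article gives no sample size, effect size or power for the before-and-after study; these are deferred until the earlier parts are done. Its figure of 960 records belongs to the current care study and has no bearing here. The check is therefore whether random assignment fits the stated structure, and how a regional rule could act.

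**1. Is a 1:1 draw possible with the same hospitals?**
Inputs from *Study population and setting*: strata of 2, 6 and 4 hospitals, and six hospitals per arm.
- 2 + 6 + 4 = 12. Every stratum is even, so each splits 1 + 3 + 2 = 6 per arm.
- Allocations with a draw within strata: C(2,1) × C(6,3) × C(4,2) = 2 × 20 × 6 = 240. Smallest two-sided randomisation p = 2/240 = 0.0083.
- Allocations with a draw within six pairs: 2^6 = 64. Smallest two-sided p = 2/64 = 0.031.

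**2. Is there room for a geographic or shared-staff constraint?**
Reaching p ≤ 0.05 needs 2/N ≤ 0.05, so at least N = 40 admissible allocations. Suppose two hospitals must be in the same arm.
- Draw within pairs, the two in different pairs: 64/2 = 32 allocations, smallest p = 2/32 = 0.0625. The 5% level can no longer be reached. If the two form one pair, no allocation is admissible.
- Draw within strata, the two in different strata: 240/2 = 120, smallest p = 2/120 = 0.017.
- Draw within strata, both in the stratum of six: C(4,1) + C(4,3) = 8 splits instead of 20, so 2 × 8 × 6 = 96, smallest p = 2/96 = 0.021.
- Draw within strata, both in the stratum of four: 2 splits instead of 6, so 2 × 20 × 2 = 80, smallest p = 2/80 = 0.025.
- Both in the university stratum of two: no allocation is admissible.

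Except in the last case, a draw within strata can absorb one such constraint. A draw within pairs cannot.

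**3. How large could the regional bias be?**
The article has no data on regional trends, so this is an assumption shown over a range. Let trends in adherence vary independently between regions with SD s. With k regions per arm and equal weights, the difference between arms has SD s × √(2/k).
- One region per arm (k = 1), for s = 2, 5, 10 points: 2.8, 7.1, 14.1 points.
- Three regions per arm (k = 3): 2 × √(2/3) = 1.6, 5 × √(2/3) = 4.1, 10 × √(2/3) = 8.2 points.
- Randomised, each of the 12 hospitals in its own region (k = 6): 1.2, 2.9, 5.8 points.

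The last line differs in kind as well as size. After a random draw this variation is part of the between-hospital error and the test allows for it. Under a regional rule it is a bias that the test does not see.

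**The case against.** The strongest reply is that the rule is ambiguous. Assigning by region within strata may mean spreading the arms over regions rather than splitting them by region. On that reading region is not confounded with the arm, and could even be better balanced than after a draw among 12 hospitals. This stands. A reader might infer that region is confounded with the strategy outright, but the sentence does not establish it. What remains is that assignment is still not random and that the text does not say which meaning applies.

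Second, the design is openly a controlled before-and-after study and claims no randomisation. That is so, and it limits the severity. The label discloses the choice but does not justify it, and the analysis section still aims at an independent effect.

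Third, keeping neighbouring hospitals in one arm may limit spill-over, which is plausible for a strategy aimed at professionals, patients and the organisation in hospitals that already collaborate in one consortium. So it cannot be said that the regional rule gains nothing. The article gives no reason, but an article may leave that to the full protocol.

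Two further inferences are tempting. One is that the matched pairs are thrown away. The pairs are described as possible and belong to the selection of hospitals, and the text is silent on whether assignment respects them. The other is that hospitals thought receptive would be steered into the strategy arm. Nothing in the rule refers to receptiveness.

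**Conclusion.** The concern holds in a limited form. The article states a non-random assignment rule, applied once participation is settled, although its own strata allow a 1:1 draw with the same hospitals and patients. Stable differences in local practice are handled by the before-measurement; differential change over time is not.

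The size depends on how region is used. If it separates the arms, a regional difference in trend adds one for one to the estimated effect. The bias SDs of 2.8 to 14.1 points are the extreme case of one region per arm, under assumed trend SDs of 2 to 10 points; they illustrate a mechanism and do not estimate the bias in this study. If region balances the arms, the bias is smaller and cannot be quantified from the document. On either reading the independent effect is not secured by the design. This is a worthwhile and cheap improvement, not a fatal flaw.

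**What to change.** Replace the assignment sentence with wording such as: *Within each of the three hospital strata, half of the participating hospitals are assigned to the strategy by a computer draw made by someone independent of the study team. Any geographic or shared-staff constraint is written down before the draw, and the number of admissible allocations is checked and recorded.* At least 40 admissible allocations should remain.

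Add to the analysis a randomisation test on hospital-level changes, computed over exactly those admissible allocations and reported beside the multilevel model.

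The cost is a few sentences and one draw, with no extra hospitals, patients or measurements. The downside is possible spill-over where neighbouring hospitals fall in different arms, which the written constraint limits.

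If randomising is not possible, state whether region balances or separates the arms, and drop the claim of an independent effect.
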